#### Informal carers

The participating patients will be asked to give their permission for approaching one of their informal carers to also participate in the study. The carers need to be in contact with the patient (physically or by telephone/email) for at least one hour a week. When the collaboration with an informal caregiver impedes the treatment process or negatively influences the safety of the patient, carers can be excluded. This will only take place after consultation with the patient.

#### Nurses

Ten mental health nurses from the experimental condition and five nurses from the control condition will be included in the study. Participation takes place on a voluntary basis. Nurses who participate in the experimental condition will receive a three-days training in providing the Collaborative Care Program. Nurses in the control condition will offer Care as Usual.

### Selection of patients

The required number of cases for a multiple case study depends upon the heterogeneity among the cases (more heterogeneity requires more cases) and is therefore arbitrary. To take into account the variety in presentation of the disorder and the variety of problems, this study will include at least sixteen patients in each condition. This adds up to 32 cases.

### Intervention

#### Collaborative Care Program

This Collaborative Care Program is developed to improve the quality of care for patients with severe personality disorders within a community mental health care setting. The expectation is that the Collaborative Care Program (1) improves quality of life, (2) reduces destructive behaviour (suicidal, self harm, aggressive or addictive behaviour) and other manifestations of the (borderline or NOS) personality disorder, (3) improves mastery of the patient, and (4) enhances satisfaction with care by both patients and informal caregivers. Finally, we aim for a positive effect on attitudes, knowledge and skills of nurses.

Collaborative Care for patients with severe borderline or NOS personality disorders consists of five integrated components (see Figure 1). The different components of the execution stage can be applied in a flexible order, dependent on the priorities in unmet needs and the preferences of the patient. Although CCP offers a goal-oriented structure, it comes to the professionalism of the nurses to adjust this structure to the preferences of the patient, the patient's cognitive capacities, and to the extent of illness insight/acceptance of each individual patient. The different components of the CCP will be briefly elucidated. The Collaborative Care Program is elaborated in a workbook for patients and nurses and in a separate manual for nurses. More detailed information about the content of the CC Program is available (see Additional file 1).

**Figure 1 F1:**
[figure not shown]
**the five integrated components of the Collaborative Care program**.

##### 1. Organization and contracting

A Collaborative Care Team will be put together for adequate coordination of care, with optimal collaboration between the main team partners: i.e. the patient, his/her informal carer(s), a psychiatric nurse and a psychiatrist and/or psychologist. Because discontinuity of care increases the risk of drop-out and a negative course of the psychiatric illness (with possible suicide as the extreme negative outcome), Collaborative Care demands pro-active collaboration between all partners to minimize this discontinuity of care. The nurse is responsible to inform and involve all those partners, whenever necessary. The execution stage of the CCP should not start before a treatment plan is established to which all collaborative partners commit [37,40,42]. Due to the ambivalent care seeking of most of the patients, this stage is therefore crucial and requires a careful preparation. This preparation stage consists of several activities (see Additional File 1).

Within Collaborative Care the patient is perceived as the one who shapes his own life, and hence his own treatment. Active involvement of the patient is required to reach the objectives of improved self management skills and shared decision making [36]. Patients, however, often have a long history of contacts with health care providers, with divergent success. To learn from previous experiences, an inventory is made of life events and of former treatments, based on the medical record. This inventory will be discussed with the patient and with the other members of the Collaborative Care Team to identify effective coping strategies with life events, effective elements in treatment, and relationships. Patients are invited to express their expectations about care providers and treatment and to speak aloud about disappointing (sometimes even traumatic) experiences, which still may hamper the relationships with care providers. Informal carers are invited to share their view upon past life events and expectations with regard to collaboration and treatment. Mutual expectations and responsibilities are made explicit between patients, informal carers and care providers, in order to promote a strong relationship [26,50]. The agreements about the collaboration are recorded in the treatment plan.

Health care needs will be assessed with the Camberwell Assessment of Needs (CAN) [51]. Based on the CAN results priorities in treatment goals will be set within the Collaborative Care Team. Unmet needs, goals and related activities are recorded in the treatment plan. In anticipation of possible crises, a crisis card will be compiled [26]. The use of a crisis card fits in the philosophy of collaborative care because it communicates that patients are (at least partly) able to cope with crisis themselves. If not, a back up of professional care is always available 24/7. The content of the crisis card is communicated with the crisis services and informal carers. Additionally, contracting will be used, based on shared decision making about the collaboration, the treatment process and the treatment plan [26,50]. The final step in the preparation stage is to confirm the goals, activities and agreements about collaboration in the treatment plans, which are evaluated every three months.

##### 2. Destructive behaviour

To reduce destructive behaviours a method of early recognition and early intervention will be implemented [26,52-54]. These destructive behaviours may have different forms: suicidal, self harm, addictive or aggressive behaviours. The central aim of the intervention strategy is the recognition of early warning signs (thoughts, feelings and/or behaviours) of the destructive behaviour of the patient. The aim is to help the patient gain a better insight in the process of destructive behaviour and to enhance coping with this behaviour. A relapse prevention plan will be drafted in which early signs are described, as well as actions how to respond to raising stress, despair and imminent crisis.

##### 3. Problem Solving Treatment

To reduce daily life problems Problem Solving Treatment (PST) will be applied [55]. The amount of daily life problems is often overwhelming in this subpopulation of patients, through which they may loose their sense of control. Learning and applying problem solving skills regarding daily problems enhances mastery and may result in a better quality of life. Mastery reflects the extent to which individuals perceive themselves in control of forces that significantly impact on their lives. PST has proven to be effective in different studies and is part of different treatments for personality disorders [50,55,56]. It is an essential element of Collaborative Care Programs [34,39,45].

##### 4. Life orientation

As counterbalance to the prominent attention to problems and destructive behaviour, the focus of CCP is also aimed at a more positive orientation in a person's life. Elements of Solution Focused Treatment will therefore be used to encounter and expand positive experiences which is expected to be stimulating for a renewed and more positive life orientation [57,58].

##### 5. Psycho-education

By means of psycho education, the patient (and their carer) is provided with knowledge about his or her psychological condition, the causes and consequences of that condition, ways of coping with it, and the treatment possibilities including the expected effects of it. Patients and their carers also will be prepared to the enduring character of the illness and to expected relapses. Psycho education is an integral element of Collaborative Care [36,39,42].

### Treatment integrity

The nurses who participate in the experimental condition will receive a three-day training program from three of the authors (BS, [name] en BK) in the principles and skills of the CC Program. During the provision of the CC Program, supervision for the nurses will be provided for continuing education on attitude and skills. Bi-weekly individual consultation and coaching (by telephone or email) will be offered based on the work sheets of the workbook and the manual to further support treatment integrity. Supervision, consultation and coaching are provided by the first author (BS).

### Control Condition

Patients in the control condition receive care as usual from their current care providers. During the study period, nurses in both conditions are not permitted to receive any extra training that might interfere with the content of the CCP.

#### Data collection

There are three measurements in this study: when participants enter the study (T0), after five months (T1) and after nine months (T2). To achieve the formulated objectives of this study, the data collection is divided into two parts. Quantitative data are collected with questionnaires to describe the outcomes of the CC Program in comparison with the CAU (summarized in table 1). Qualitative data, such as interviews, and records of the supervision sessions are used to analyse the implementation process of the application of the CCP in comparison with CAU. Data will be collected among patients, their informal carers and nurses, as mentioned below.

**Table 1 T1:** Summary of the used questionnaires.

	Questionnaires		
Outcome indicator	*Patients*	*Informal caregivers*	*Nurses*
Quality of Life	▪ Manchester Short Appraisal (MANSA)		
Psychopathology	▪ Borderline Personality Disorder Severity Index (BPDSI) ▪ Structured Clinical Interview for DSM-IV Personality Disorders (SCID-II)		
Destructive behaviours	▪ BPDSI ▪ Beck Scale for Suicide Ideation (BSSI) ▪ CAGE questions-adapted to include drugs (CAGE-AID)		▪ Suicide Behaviour Attitude Questionnaire (SBAQ) ▪ Attitudes Towards Deliberate Self-Harm Questionnaire (ADSHQ)
Health care use	▪ Trimbos/iMTA questionnaire for Costs associated with Psychiatric Illness (Tic-P)		▪ process forms
Psychosocial symptoms	▪ Brief Symptom Inventory (BSI)		
Satisfaction	▪ Consumer Quality-index (CQ-index)	▪ CQ-index	
Therapeutic Alliance	▪ *S*cale *t*o *A*sses Therapeutic *R*elationships in Community Mental Health Care (STAR)		▪ STAR
Mastery	▪ Pearlin Mastery Scale (PMS)		
Involvement/social support		▪ Involvement Evaluation Questionnaire (IEQ)	

### Questionnaires for patients

#### Sample characteristics

Information will be gathered at baseline on demographic characteristics (age, gender, education level, marital status, work and ethnicity), history of illness, current medication use and diagnostic characteristics (DSM-IV Axis II by means of the Structured Clinical Interview for DSM-IV Personality Disorders (SCID-II) [59], the other axes are obtained from the medical records).

#### Primary outcome indicators

##### Quality of life

The Manchester Short Appraisal (MANSA) is a self-report scale, which measures quality of life. It is a short version (16 items) of the Lancashire Quality of Life Profile (LQoLP). Priebe et al. [60] found an adequate correlation between the results on both QoL scales.

##### Borderline Personality Disorder Severity Index (BPDSI)

The BPDSI is a DSM-IV BPD criteria-based semi-structured interview consisting of 70 items. It represents the current severity and frequency of the DSM-IV BPD manifestations. This instrument showed excellent psychometric features [5,49,61].

#### Secondary outcome and process indicators

##### Destructive behaviours

Four frequently observed destructive behaviours are measured. The BPDSI contains subscales measuring parasuicidal behaviour, including self harm, and aggressive behaviour. Additionally, the Beck Scale for Suicidal Ideation is used to measure suicidal thoughts, ideas and behaviours. It is a self-report scale of 21 items and has good psychometric properties [62,63]. The CAGE questions Adapted to Include Drugs (CAGE-AID) is a composed questionnaire describing the consequences of alcohol and drugs use [64].

##### Health care use

The Trimbos/iMTA questionnaire for Costs associated with Psychiatric Illness (TiC-P) is developed to measure health care consumption (part 1) and costs (part 2) [65]. In this study only part 1 of the questionnaire, concerning health care consumption, is used.

##### Psychosocial symptoms

The Brief Symptom Inventory (BSI) is a shorted version of the SCL-90 with 53 items (self report). Reliability and validity are almost identical to the SCL-90 [66].

##### Patient satisfaction

For the measurement of patient satisfaction the Consumer Quality-Index (CQ-Index) for outpatient mental health care is used [67]. It comprises items about information provision, involvement in treatment decisions, expertise and availability of professionals, and outcomes of treatment.

##### Quality of the therapeutic relationship

The *S*cale *t*o *A*sses Therapeutic *R*elationships in Community Mental Health Care (STAR) is a questionnaire which measures the quality of the therapeutic relationship [68]. A professional and patient version of the scale is available and a Dutch translation of this questionnaire will be used in this study.

##### Mastery

Pearlin and Schooler's Personal Mastery Scale (PMS, 1978) is a commonly used instrument to measure the external locus of control, also referred to as mastery. It consists of five items on a four point Likert scale (self report). The PMS has adequate validity and reliability [69,70].

### Questionnaires for informal carers

#### Process indicators

##### Carer satisfaction with care

For the measurement of carer satisfaction an adapted version of the CQ-index is used [67].

##### Involvement/social support

The Involvement Evaluation Questionnaire (IEQ) [71,72] is a self report list of 81 items, divided among seven sections. It measures consequences of care giving in informal carers.

### Questionnaires for nurses

#### Sample characteristics

Information is gathered at baseline on demographic characteristics (age, gender, education), working experience in mental health care and with this specific patient population.

#### Process indicators

##### Quality of the therapeutic relationship

Complementary to the patient's view on the quality of the therapeutic relationship, nurses will be asked to fill in the professional version of the STAR [68].

##### Attitudes towards destructive behaviours

The Suicide Behavior Attitude Questionnaire (SBAQ) consists of 21 items to be scored on visual analogue scales. Three subscale are differentiated: (1) feelings in relation with the care for suicidal patients, (2) professional skills and (3) the right for suicide [73].

Attitudes towards self harm are measured with the Attitudes Towards Deliberate Self-Harm Questionnaire (ADSHQ) as developed by McAllister *et al*. [74].

#### Process forms

Nurses in both conditions fill in process forms in which the number and content of contacts will be registered. In the experimental group items are added which provide additional insight in the treatment integrity. The process form follows the elements of the intervention and will systematically remind them on the structure and objectives of the CC Program.

### Qualitative data

#### Interviews

Individual interviews with patients, their carers and nurses (in this fixed order) will take place after the follow up measurement (T2). In the in-depth interviews the process of the application of the CC Program, and the relationship between this application and outcomes will be examined and compared to the application of CAU. In the interviews participants are first asked to reflect on the quantitative outcomes and on which changes they perceive as most beneficial. Subsequently, the underlying (neutrally formulated) principles of the CCP will be discussed, e.g. problem solving, coping with destructive behaviour, quality of the therapeutic relationship, and self-management. Next, exemplifications will be asked to identify characteristics of these principles which may explain the individual outcomes. Finally, the participants are asked to identify hampering or fostering components in the application of CCP or CAU.

The interviews will be audio taped and transcribed verbatim. The data will be analysed using WINMAX qualitative text analysis software. The credibility and dependability of the data will be ensured by peer debriefing, member checking, and thick descriptions [75].

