**Methods/design:**

Quantitative and qualitative data are combined in a comparative multiple case study. This makes it possible to test the feasibility of the CCP, and also provides insight into the preliminary outcomes of CCP. Two treatment conditions will be compared, one in which the CCP is provided, the other in which Care as Usual is offered. In both conditions 16 patients will be included. The perspectives of patients, their informal carers and nurses are integrated in this study. Data (questionnaires, documents, and interviews) will be collected among these three groups of participants. The process of treatment and care within both research conditions is described with qualitative research methods. Additional quantitative data provide insight in the preliminary results of the CCP compared to CAU. With a stepped analysis plan the 'black box' of the application of the program will be revealed in order to understand which characteristics and influencing factors are indicative for positive or negative outcomes.

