## Methods/Design

### Design

A comparative multiple case study may be used for the thorough evaluation of complex intervention programs [46-48]. The research generates descriptive and explanatory data regarding treatment processes and outcomes of the intervention program. Different perspectives are integrated in the evaluation: the perspective of patients, their informal carers and nurses. In our multiple case study two treatment conditions will be compared: one functions as the experimental condition in which the Collaborative Care Program is provided; the other condition functions as the control condition in which Care as Usual (CAU) is offered. Different types of data collection will be used: questionnaires, documents, and interviews. A case is defined as the treatment process of one patient in which integrated data from the three perspectives (patient, informal carers and nurse) concerning the application and the outcomes of the CCP or CAU will be gathered and analysed.

Within a comparative multiple case study, data are analyzed at the individual case level, group level, as well as between groups level [46-48]. The process of treatment and care within both research conditions is described with qualitative research methods. Additional quantitative data provide insight in the preliminary results of the CCP compared to CAU. By means of data triangulation, the connection between the application and the preliminary outcomes of the Collaborative Care Program will be explained in comparison with Care as Usual. With a stepped analysis plan the 'black box' of the application of the intervention program will be revealed in order to understand which characteristics and influencing factors are indicative for positive or negative outcomes.

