### Qualitative analyses

To describe and understand the process of the application of the CCP versus CAU, the qualitative interviews with patients, their carers and nurses will be analyzed, following the three steps as described above. Beforehand, as preparation for the interviews, the supervision records will be analysed and the quantitative outcomes will be assessed at an individual level.

For the *within case analyses*, the data from the interviews are coded and categorized following the structure as described above. As said, for the *cross case analysis *the participants of both research conditions are divided in three subgroups. Based on the interview data, similarities and differences in the process of the application are described for the three subgroups. The different perspectives of patients, informal caregivers and nurses will be taken into account in this analysis. The degree, to which these perspectives differ from each other, might be indicative for the obtained outcomes. For the *cross case synthesis*, the data from the interviews will be examined to identify group differences between the two research conditions: Which statements do participants make about the underlying principles of the CCP? How do they value these principles? How do they value the outcomes of the CCP resp. CAU?

A content analysis of the supervision records will be performed to identify hampering and fostering characteristics in the process of the application of the CCP from a nursing perspective. For the *within case analysis *this information will be used as a preparation for the interviews. When performing the *cross case analysis and synthesis*, this information exemplifies and partially explains observed outcomes of the application of CCP.

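### Nurse and carer interviews open on quantitative outcomes whose primary measures come only from the patient, which can anchor the accounts whose divergence is later used to explain outcome

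*Protocol article*

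**What the plan says.** In the protocol article, the Interviews section under Qualitative data plans separate interviews after the T2 measurement, with the patient first, then the carer, then the nurse. The opening task is common to all: "In the interviews participants are first asked to reflect on the quantitative outcomes and on which changes they perceive as most beneficial". Later in the same interview, informants are asked for examples that could account for the outcomes of the individual case.

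The Qualitative analyses section states what is prepared beforehand: "the supervision records will be analysed and the quantitative outcomes will be assessed at an individual level". The same section describes the cross-case analysis, which draws on the interview data and takes the three perspectives into account. It adds: "The degree, to which these perspectives differ from each other, might be indicative for the obtained outcomes".

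Two other places settle who and what is meant. The Abstract (Methods/design) names patients, carers and nurses and says: "Data (questionnaires, documents, and interviews) will be collected among these three groups of participants". The Design section gives the unit of analysis: "A case is defined as the treatment process of one patient in which integrated data from the three perspectives".

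**The concern.** The article wants to learn something from how far the patient, carer and nurse differ in what they say. That requires each account to be formed, at least at the start, without reference to the others. If the interviewer opens by putting the case's quantitative outcomes to the nurse or carer, and those outcomes are largely the patient's, the later accounts start from the patient's position. Informants tend to adjust towards results they have been told and to build explanations around them. Measured disagreement then shrinks for a reason unrelated to the care process.

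What is at stake is the third objective, explaining which characteristics of the program go with good or poor outcomes, and the triangulation announced under Design. A secondary matter is the care relationship: the patient's ratings of the therapeutic relationship and of the care received are among the quantitative data, and the wording does not set them apart.

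**Working it through.** There is no sample-size or error-rate figure to reproduce. The check sets the sections side by side and counts instruments and interviews.

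**1. Who reflects on the outcomes.** The Interviews section says participants, and the Abstract uses that word for all three groups. Nothing in the section limits the opening task to patients or to the informant's own scores.

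**2. Which outcomes.** They are prepared per individual before the interviews (Qualitative analyses), and a case is one patient's treatment process (Design). The natural reading is case-level outcomes.

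**3. Whose scores these are.** Instruments in Table 1, each counted once per respondent group:

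- Patients, 10: MANSA, BPDSI, SCID-II, BSSI, CAGE-AID, TiC-P, BSI, CQ-index, STAR, PMS.
- Carers, 2: CQ-index, IEQ.
- Nurses, 4: SBAQ, ADSHQ, STAR, process forms.

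Patient share: 10 / (10 + 2 + 4) = 10/16 = 62.5%. Without the SCID-II (gathered at baseline) and the process forms: 9/14 = 64.3%. Under the text headings for primary outcomes and for secondary outcome and process indicators, the share is 9/9; carer and nurse measures appear under process indicators. On either count, both primary measures (MANSA, BPDSI) are patient-only.

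**4. What nurses and carers can reflect on from their own data.** For the therapeutic relationship, "nurses will be asked to fill in the professional version of the STAR", so the nurse has a score of her own. The SBAQ and ADSHQ measure the nurse's attitudes. A carer has the CQ-index and the IEQ. None of these gives a quality-of-life or severity result for the patient. To reflect on those outcomes, a nurse or carer must be told something of the patient's results or rely on impression; the article does not say which.

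**5. What can be affected.** Questionnaires are taken at T0, five months (T1) and nine months (T2), and interviews follow T2. Paired questionnaire measures (patient and nurse STAR, patient and carer CQ-index) are therefore already recorded. Only the interview accounts are exposed, and these are the source for the comparison of perspectives.

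**6. How many interviews.** At 16 + 16 = 32 cases and three informants per case, 32 × 3 = 96 interviews, of which 32 × 2 = 64 are with a nurse or carer. This is a ceiling at the planned minimum sample. It assumes a participating carer for every case and one nurse interview per case. Carers need the patient's permission and can be excluded, and 10 + 5 = 15 nurses serve all cases, so interviews may be combined.

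**7. Strength of anchoring.** If an informant moves a fraction k of the way towards the patient's results, the observed difference falls to (1 − k) of its original size. The document gives no k, and an assumed value would only return itself, so none is offered.

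**The case against.** The strongest reply is that starting from outcomes is deliberate. The study aims to link process to outcome, and informants who do not know the outcome cannot help to explain it. Limiting nurses and carers to their own scores would work against the third objective. This stands, and it is why the remedy concerns order and separation within the interview, not a ban on discussing outcomes.

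A reader might infer that patient STAR, CQ-index, suicidality or substance-use scores are in fact disclosed to nurses and carers. The article does not say so. Individual assessment before the interviews also fits an interviewer preparing a topic list. Restrictions may stand in the interview guide or information letter, which a journal article commonly leaves out, and their absence here is no finding.

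A reader might also infer that nearly all outcomes are the patient's. That depends on the count: 10 of 16 instruments in Table 1, and all nine under the text headings. Table 1 also lists two nurse attitude scales in its row on destructive behaviour.

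A third tempting inference is that the three perspectives altogether lose their independence, or that patients soften their questionnaire answers. The first goes too far, because the questionnaires precede the interviews and the interviews are individual. The second requires patients to expect disclosure, and nothing in the article says that they are told to. Harm to the care relationship likewise depends on a disclosure that is not stated.

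What survives is narrower: the stated opening task, applied to nurses and carers, precedes the accounts that the analysis will compare.

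**Conclusion.** The point holds in limited form. As written, the interview procedure can anchor nurse and carer accounts given after T2 to the patient's results, and the analysis then reads meaning into how much those accounts differ. The likely effect is that disagreement is understated. At most 64 of 96 interviews are exposed, at 32 cases with one carer and one nurse interview each; the degree of anchoring is unknown.

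The conclusion rests on two readings: that participants in the Interviews section means all three groups, as in the Abstract, and that the difference between perspectives is judged from the interviews, as Qualitative analyses indicates. It does not extend to the T0 to T2 questionnaire scores or to the group comparisons based on them, and it does not establish that any patient score is shown. It is worth correcting because the comparison serves a stated objective and the change is small.

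**What to change.** Amend the Interviews section as follows.

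1. Nurses and carers first describe, without being shown patient scores, which changes they saw in the patient.
2. That unprompted part is the material for the comparison of perspectives under Qualitative analyses; say so there.
3. Outcomes are discussed with nurses and carers only afterwards, as the explanatory part of the interview.
4. The patient's research ratings of the relationship and of care (STAR, CQ-index) are not passed to the nurse or carer. Changing the order alone would not secure this.

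No rule is proposed for suicidality or substance-use results, since their handling is a clinical matter; the documents should only say how they are treated.

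The cost is some wording in the interview guide, slightly longer interviews, and less direct comment from nurses and carers on specific scores.
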